|------------------------------------------------------------------------------|---------------------------------------------------------------------------------------------------------------------------------------------------------------------------------------------------------------------------------------------------------------------------------------------------------------------------------------------------------------------------------------------------------------------------------------------------------------------------------------------------------------------------------------------------------------------------------------------------------------------------------------------------------------------------------------------------------------------------------------|
| Summary of secondary mechanistic objective (for full definition see Table 3) | To describe the effect of POCT RM results on Study Clinician and participant beliefs in the necessity and benefits, of prescribing antibiotics, and confidence in the value of the POCT RM                                                                                                                                                                                                                                                                                                                                                                                                                                                                                                                      |
| Summary of tertiary mechanistic objectives (for full definition see Table 3) | 
 
1. To investigate whether control group Study Clinician antibiotic prescribing is better than chance compared to microbiological testing
 
2. To explore the relationships between baseline symptoms and signs, POCTRM result, antibiotic consumption and participant reported: (i) symptom severity at days 2 to 4; and (ii) duration of moderately bad (or worse) symptoms
 
3. To compare POCTRM results at GP practices with POCTRM results at the central research laboratory (intervention group only), and between POCTRM results at central research laboratory with extended central research laboratory testing
 
 |
| Trial duration                                                               | Funding start date: 1 April 2022. Anticipated duration: 38 months (total; subject to change). Anticipated end date: 31 May 2025 (subject to change)                                                                                                                                                                                                                                                                                                                                                                                                                                                                                                                                                                                   |

Figure 1: Trial Flowchart

[figure not shown]

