| Inclusion criteria    | 
Eligibility will be assessed by GP practice and participant.
 
GP practices will be eligible if:
 
 
Served for routine laboratory testing by one of the following four hospitals: Southmead (North Bristol), the Bristol Royal Infirmary, Royal United Hospitals (Bath) and Weston General. GP practices out of this area are eligible if served by a hospital that can accept trial samples within 24 hours and then transfer them to the central laboratory within 24 hours, or are willing to send samples via courier to the central laboratory within 24 hours.
 
Have a clean, well ventilated area for the Biofire® FilmArray® Torch 1 machine, not in close proximity to sources of strong electromagnetic radiation, and with the following dimensions: depth ≥77cm, width ≥49cm, height ≥30cm and at least 2.6cm between the rear panels and any other surfaces
 
 
Participants will be eligible if:
 
 
Aged ≥12 months on the day of presentation to primary care
 
Presenting to primary care for the first time in this episode, and within 21 days of illness onset, with a Study Clinician suspected acute respiratory infection. Symptoms may include one or more of: sore throat, runny nose, earache, cough, sputum, wheeze or shortness of breath.
 
Presentation is face-to-face, via telephone or online
 
 |

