## 6.6 Randomisation (Day 1)

### Figure 1, Step 4

Participants will be individually randomised 1:1 to intervention (GP POCTRM test) or control (No GP POCTRM test) using an internet-based randomisation system developed and maintained by Sealed EnvelopeTM. Randomisation will be stratified by age (<16 years vs. ≥16 years) and chronic lung disease (present vs. absent). It will not be possible to blind the allocated randomisation group since the subsequent processes for each group differ.

The Study Champion or Clinician randomises participants and immediately informs (if necessary) the Study Clinician which group the participant has been allocated to.

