### 2.10.1. CLINICAL PRIMARY OUTCOMES

| Primary Outcome        | Type   | Outcome detail                                                                                                                                                                 |
|------------------------|--------|--------------------------------------------------------------------------------------------------------------------------------------------------------------------------------|
| Antibiotic prescribing | Binary | The primary outcome is whether an antibiotic is prescribed (included delayed prescribing) for a RTI on day 1. Study clinician report on Appointment 2 case report form. |

The study clinician will collect the following data onto the **study case report form**: eligibility criteria, consultation format, signs and clinical measurements at presentation, diagnosis, medical history, previous prescription of antibiotic for current episode of RTI, POCT result, details of any prescription at appointment two (= primary outcome).

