#### 4.5. ANALYSIS OF THE KEY SECONDARY OUTCOME

The key secondary outcome, participant reported mean symptom severity on days 2 to 4, will be compared between the two allocated groups, POCT versus no POCT, using a mixed linear regression model with covariates distinguishing the allocated groups, the two age groups (< 16 years old versus ≥ 16 years old) and chronic lung disease status (present versus absent), and a random effect at the participant level to accommodate the correlation between the three repeated responses per participant. Keeping the symptom scores separate as three repeated measures, rather than taking an average symptom score over the three days, provides greater transparency in the accommodation of patients who have reported symptoms on only one or two of the three days.

For comparability with previous studies in this area, the estimator will be the difference between the allocated groups in the average symptom score over days 2, 3 and 4. The coefficient of the covariate distinguishing the allocated groups, described in the previous paragraph, will provide this estimator. The distribution of residuals will be checked, and if markedly non-normal, the use of bias-corrected and accelerated bootstrap confidence intervals will be considered.

If a one-sided 95% confidence interval excludes increases of 20% or greater in the mean symptom score reported by the group allocated to POCT, then the POCT group will be considered non-inferior. A two-sided 95% confidence interval and p-value will also be presented to allow comparison with other studies, and inference about superiority of the POCT group in the event that non-inferiority is demonstrated (**Table 3**, see Section 5).

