#### 4.7. ANALYSIS OF THE SECONDARY OUTCOMES

The primary outcome analysis will be adapted to the secondary clinical outcomes by the choice of a suitable regression model. Effect sizes, 95% confidence intervals, and p-values will be presented (**Table 3** and **Table 4**, see Section 5).

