| Other symptom measures                           | Mean (SD), n                 | Mean (SD), n            | Difference in meansc
(95% confidence interval) | P value |
| Duration of moderately bad, or worse, symptoms          | X.X (X.X), X                        | X.X (X.X), X                   | XX.XX (XX.XX, XX.XX)                                                 | 0.XXX          |
| Time to return to usual activities (adults 16+ years)   | X.X (X.X), X                        | X.X (X.X), X                   | XX.XX (XX.XX, XX.XX)                                                 | 0.XXX          |
| Time to return to usual activities (children <16 years) | X.X (X.X), X                        | X.X (X.X), X                   | XX.XX (XX.XX, XX.XX)                                                 | 0.XXX          |
| Overall symptom duration                                | X.X (X.X), X                        | X.X (X.X), X                   | XX.XX (XX.XX, XX.XX)                                                 | 0.XXX          |
|                                                         | n/N (%)                      | n/N (%)                 | Odds ratioa
(95% confidence interval)          | P value |
| Participant experiences worsening symptoms              | XX/XXX (XX%)                        | XX/XXX (XX%)                   | XX.XX (XX.XX, XX.XX)                                                 | 0.XXX          |

a. All estimates adjusted for participant age and chronic lung disease status

b. One-sided 95% confidence interval, for establishing non-inferiority, presented in the text

c. Bias-corrected and accelerated bootstrap confidence intervals, non-parametric p-value

**Table 4.** Further healthcare contacts post-randomisation

|                                                                                                  |    | Intervention
N (%) | Control
N (%) | Odds ratio*
(95% confidence interval) | P value* |
|--------------------------------------------------------------------------------------------------|----|-----------------------|------------------|------------------------------------------|----------|
| Number (%) of patients hospitalised for RTI one or more times between appointment two and day 28 |    | XX (XX%)              | XX (XX%)         | XX.XX (XX.XX, XX.XX)                     | 0.XXX    |

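### Days since illness onset, which can run to 21 at entry, is neither reported at baseline nor used as a covariate for the symptom outcomes: a modest loss of precision and description, not a bias

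*Combined protocol and SAP*

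**What the plan says.** The entry window is in the protocol's Trial Summary and section 5.2.2, and again in SAP 2.3: "Presenting to primary care for the first time in this episode, and within 21 days of illness onset".

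Time since onset is then absent from each place where it could be used or shown:

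- **Strata (protocol 6.6):** "Randomisation will be stratified by age (<16 years vs. ≥16 years) and chronic lung disease (present vs. absent").
- **Key secondary model (SAP 4.5):** "covariates distinguishing the allocated groups, the two age groups (< 16 years old versus ≥ 16 years old) and chronic lung disease status", plus a participant random effect.
- **Other secondary outcomes (SAP 4.7):** "The primary outcome analysis will be adapted to the secondary clinical outcomes by the choice of a suitable regression model". No further covariate is named.
- **SAP Table 3, footnote a:** "All estimates adjusted for participant age and chronic lung disease status". The duration rows carry footnote c, which specifies bootstrap intervals and a non-parametric p-value.
- **SAP Table 1:** demographics, history, clinical measures, signs, diagnosis and overall assessment, with no row for illness duration.
- **Case report form contents (SAP 2.10.1):** "eligibility criteria, consultation format, signs and clinical measurements at presentation, diagnosis, medical history", then earlier antibiotics for the episode, the test result and the prescription. An onset date is not named, though the eligibility check implies that onset was judged.

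SAP 4.6 item 2 adds unbalanced baseline variables in a sensitivity analysis of the primary and key secondary outcomes only. For continuous variables the trigger is a difference in means above 0.5 SD.

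**The concern.** The symptom outcomes are how the trial checks that fewer antibiotics do no harm, so their precision matters. Overall symptom duration in SAP 2.10.2 counts diary days, and the diary starts on Day 1. It is therefore the illness remaining at entry. Two people with the same 20-day illness who enter on day 2 and day 15 score 18 and 5 days, a gap of 13 days unrelated to allocation. A variable judged before randomisation that may account for some of that spread is left unused, and nothing in the planned tables shows whether the arms entered at a similar stage of illness.

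**Working it through.** **1. The plan's own figure.** Protocol 10.1.1 and SAP 2.7 give a coefficient of variation of 0.7, a 20% margin, one-sided 5% and 90% power. On the log scale the SD is √ln(1 + 0.7²) = 0.6315 and the margin is ln 1.2 = 0.1823.

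n per group = 2 × (1.645 + 1.282)² × 0.6315² / 0.1823² ≈ 206, with 90.1% power at 206. This reproduces the plan. No covariate gain is built in, so leaving out days since onset takes nothing from the stated power.

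**2. Gain for days 2 to 4 severity.** If days since onset correlates r with the outcome, given the existing covariates, the residual SD is multiplied by √(1 − r²). The documents give no r, so a range is shown.

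| Assumed r | Interval width | Power at 206 per group | n per group for 90% |
|---|---|---|---|
| 0 | ×1.000 | 90.1% | 206 |
| 0.1 | ×0.995 | 90.3% | 204 |
| 0.2 | ×0.980 | 91.1% | 198 |
| 0.3 | ×0.954 | 92.3% | 187 |
| 0.4 | ×0.917 | 94.0% | 173 |
| 0.5 | ×0.866 | 95.9% | 155 |

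**3. Gain for overall symptom duration.** Every input here is assumed. Total illness T is lognormal (median 14 to 25 days, log-SD 0.3 to 0.6). Presentation day P is gamma (mean 5 to 7, SD 4 to 5), limited to P ≤ 21 and P < T. The outcome is min(T − P, 28).

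- With T and P drawn independently apart from that limit, P explains about 3% to 28% of the variance, and about 14% in a middle case (median 18, log-SD 0.4).
- If late presenters have longer illnesses, the middle case shrinks. With a latent correlation between T and P of 0.2, 0.3 or 0.4, it falls to about 7%, 4% or 2%.
- With log-SD 0.6 and a latent correlation of 0.3 it is close to zero.

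In extra diaries, on 2 × 206 = 412, the gain is 412 × (1/(1 − R²) − 1):

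- R² = 0.02: about 8
- R² = 0.07: about 31
- R² = 0.14: about 67, an interval about 7% narrower since √0.86 = 0.927
- R² = 0.28: about 160

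The conversion assumes a linear model, so it is only a guide to a bootstrap analysis.

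**4. The imbalance trigger.** The standard error of a standardised difference is √(2/n).

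- 206 per arm: 0.5/√(2/206) = 5.07, a two-sided chance of about 4 × 10⁻⁷.
- 257 per arm (514/2): 0.5/√(2/257) = 5.67, about 1 × 10⁻⁸.

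The rule would in practice never bring the variable in, and a variable missing from Table 1 may not be looked at in any case.

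**The case against.** Much of the case on the other side stands.

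- **Strength of the relation.** A reader might infer that time since onset is a large, known source of variation. The documents neither say so nor give a figure, and the calculation for duration depends heavily on whether late presenters have longer illnesses.
- **Scope of the duration figures.** A reader might infer that every duration outcome is simply the illness left after Day 1, the more so because protocol Table 1 defines several of them by a last day. SAP 2.10.2 defines them otherwise. Moderately bad symptoms are measured by the longest continuous spell, which need not begin on Day 1, and return to usual activities is zero when the item is below 3 at baseline. The figures in step 3 do not carry over directly to either.
- **Bias or lost power.** Chance imbalance in stage of illness is random variation that the confidence interval already covers. It is not an added bias, and the key secondary outcome is not underpowered.
- **Availability.** Eligibility needs only a judgement that onset was within 21 days. The form itself is not in the documents, so whether an exact day is recorded cannot be settled.
- **Tertiary objective 2.** It is tempting to fault this analysis ("To explore the relationships between baseline symptoms and signs" with the test result, antibiotic use and outcome) for omitting stage of illness. The SAP's supplementary materials place it outside this plan, so its covariates are simply not yet specified.
- **A better covariate may exist.** The baseline symptom score is collected in Trial Diary Part A (protocol 6.4) and is also unused. What onset adds beyond it has not been estimated.

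None of this explains why stage of illness goes unreported, or supplies a working route to adjustment.

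**Conclusion.** The gap is real and cheap to close, and its consequences are modest. Days since onset is missing from the strata, the baseline table and the symptom models, and the sensitivity analysis that might add it will not fire. The cost is forgone precision and an incomplete account of the participants; the randomised comparisons remain valid.

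For days 2 to 4 severity the gain is small, with intervals about 0.5% to 5% narrower if r lies between 0.1 and 0.3. A material gain would need r of about 0.4 or more. For overall symptom duration the variable might explain anything from almost nothing to about 28% of the variance, depending on the spread of illness length and on how it relates to time of presentation. All of these rest on stated assumptions, because the documents supply no estimate.

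**What to change.** 1. Record days since onset at Appointment One alongside the eligibility check, or use it if it is already recorded.
2. Add it as a row in SAP Table 1.
3. Before unblinded review, pre-specify it as a continuous covariate for overall symptom duration and the other symptom outcomes, together with the baseline symptom score from the Trial Diary. SAP section 1 allows amendments that are described and justified in the final report.
4. Say in Table 3, footnote c, how covariates enter the bootstrap intervals and the non-parametric p-value.
5. Carry the variable into the separate plan for tertiary objective 2. That analysis does not rest on random allocation, and stage of illness could relate both to virus detection and to how soon symptoms end.

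The cost is at most one form field, one table row and one covariate. Recalled dates carry error, but a date recorded before randomisation cannot be influenced by allocation. SAP 4.6 already names two practices with low diary completion, so recruitment was well under way when it was written. If onset was not captured for people already recruited it cannot be recovered, and the report should state that limitation.

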## 1. BACKGROUND AND RATIONALE

Respiratory tract infections (RTIs) are the most common problem managed by health services internationally. In the UK, GPs and primary care nurses (from here on ‘clinicians’) treat over 50% of RTIs with antibiotics, with 50% of these considered inappropriate, and despite strong evidence that the majority of patients do not benefit. Overprescribing results in unnecessary side effects, depletion of normal flora, encourages patients to seek help for similar future illnesses, and fuels antimicrobial resistance (AMR), regarded as a top 10 threat to global public health. High treatment rates are attributed to clinician uncertainty regarding patients’ microbiological diagnosis and clinical prognosis, leading to ‘just-in-case’ defensive prescribing.

One potential solution, strongly endorsed by Lord Jim O’Neil in 2016, the 2019 UK Government 5-year AMR action plan, and the 2020 Wellcome Trust AMR report, is point-of care-testing (POCT). These ‘medical tests at the time and place of patient care’, are attractive to primary care because laboratory distances and procedures mean results are not available in time to inform prescribing decisions: typically 24 hours for blood and up to 72 hours for microbiological tests.

The C-reactive protein (CRP) point of care blood test measures the host inflammatory response to infection. They have been shown in randomised controlled trials (RCTs) to reduce antibiotic prescribing for adults with acute lower RTIs by 15% to 22%. However, despite National Institute for Health and Care Excellence (NICE) recommending its use in 2015 for patients with suspected pneumonia, primary care uptake remains stubbornly low. In a recent editorial we speculate that in addition to the ‘who pays?’ question, this could be because clinicians are unclear how the test works (an elevated CRP does not mean the infection is bacterial). We also observe that CRP effectiveness could be due to nothing more than the low prevalence of elevated CRP in primary care (often not reported) favouring ‘no-prescribing’ decisions in up to 90% of consultations.

Respiratory microbiological POCTs (POCTRMs) use a polymerase chain reaction (PCR) to detect viruses and bacteria from respiratory tract samples in as little as 45 minutes. They can be considered to be singleplex, duplex or multiplex according to the number of microbes being tested. Until recently, most systems were single/duplex, testing for Influenza A/B and/or Respiratory Syncytial Virus (RSV), but the Severe Acute Respiratory Syndrome Coronavirus 2 (SARS-CoV-2) pandemic has accelerated investment in multiplex POCTRM technology, with the latest equipment able to test for the presence of multiple viruses (including SARS-CoV-2) and bacteria. Importantly, the regulatory requirements for new POCTRMs are significantly lower than for new drugs: manufacturers have only to demonstrate they replicate standard laboratory testing. But prior to adoption, before equipoise is lost, evidence is needed from independent clinical trials to show safety and efficacy and later clinical and cost-effectiveness.

POCTRMs are being increasingly used in hospitals to assist with ‘bubbling’ e.g. patients with/out SARS-CoV-2 and RSV and antibiotic prescribing decisions. Multiplex POCTRMs have been shown in two Emergency Department RCTs and two observational ward-based before/after comparisons to reduce hospital admission times and durations of antibiotic courses, with only one showing reduced overall antibiotic prescribing. None reported patient symptom outcomes.

To ensure a complete understanding of the primary care POCTRM literature we conducted a systematic review, searching Medline, Embase and Cochrane (any language) between January 2000 and December 2020. We found a systematic review (search to September 2017) reporting ten studies all investigating the effects of duplex POCTRMs testing for Influenza A and B, and/or RSV, but none reporting the use of multiplex POCTRMs. None reported if the POCTRM improved clinical outcomes, with most reporting technical aspects such as turn-around time and test accuracy.

We found two further observational studies not reported in the systematic review. The first, conducted in six UK GP practices showed a singleplex Influenza POCTRM was acceptable to clinicians and had potential to reduce antibiotic (and increase antiviral) prescribing. The other, conducted in a single Dutch GP practice used a multiplex POCTRM (the mariPOC® Respi, providing results for nine respiratory viruses in two hours), showed the test was acceptable to clinicians and found clinically useful positive and negative predictive

values for Influenza A and B, and RSV (PPV range 87% to 100%, NPV 94 to 97%). Both studies concluded RCTs are needed to demonstrate impact on antibiotic prescribing and patient outcomes.

We conducted a mixed-methods feasibility study to investigate the use and acceptability of a multiplex POCTRM. Twenty clinicians from four GP practices used the POCTRM in 93 participants during a single winter. It was used in around one third of potentially eligible patients, 72% of swabs were processed in <4 hours, 90% in <24 hours with a median set-up time of 2.7 minutes. Tests detected  $\geq 1$  virus in 58% of samples, no pathogen in 37%, atypical bacteria in 2%, while 3% were inconclusive. Antibiotics were prescribed to 35% of patients with no pathogen detected and 25% with a virus. Post-test clinical diagnoses changed in 20%, and diagnostic certainty increased ( $p=0.02$ ), more so when the test detected a pathogen than not ( $p<0.001$ ). Clinicians predicted decreased antibiotic benefit post-test ( $p=0.02$ ). The 22 semi-structured qualitative interviews with healthcare professionals showed the test was easy to use and well-liked but limited by time to result and the absence of testing for typical respiratory bacteria.

None of the studies considered or evaluated the short and long-term effects of POCTRM testing on clinician and patient beliefs and behaviour, and how these changes may mediate the effect of POCTRM testing on prescribing.

We believe this is the first RCT proposed in primary care to investigate: if a multiplex POCTRM can reduce antibiotic prescribing; its effects on patient outcomes; and use of mixed-methods to directly examine hypothesised behaviour change mechanisms.

